### Outcomes and endpoints

#### Primary outcomes

Primary outcomes will be assessed at the 4 week follow-up visit. Primary endpoints include:Physical performance according to the Rivermead motor assessment (RMA) *gross function* scale;Muscle strength in a maximum hand grip strength test.

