### Sample size calculation and statistical analyses

A total of 110 patients is planned to be enrolled in the study. A prospective sample size calculation has been performed based on observational data from our study centre. A sample size of 55 in each group will have 80 % power to detect a clinically relevant difference in Rivermead Motor Assessment Gross Function scale improvement between the groups of 1.5 points and a clinically relevant improvement of handgrip strength. The analysis of primary endpoints will use the principle of intention- to-treat. The carry-forward principle will be adopted for unavailable or missing data. Treatment effect will be assessed by unpaired comparison of both treatment arms for the change from baseline using the Student t-test. A significance level of α < 0.05 will be specified to indicate statistical significance. Secondary endpoints will be analyzed using standard statistical methods. For safety endpoints Chi-squared test of Fisher’s Exact test will be used for event rates (e.g., death, re-stroke, hospitalization, cardiovascular event)

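### Two primary endpoints share one 0.05 level with no rule for combining them, so either the 5% error rate or the 80% power is not secured

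*Protocol article*

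**What the plan says.** Under Primary outcomes, the protocol article fixes the time point, "Primary outcomes will be assessed at the 4 week follow-up visit", and lists two endpoints: "Physical performance according to the Rivermead motor assessment (RMA) *gross function* scale" and "Muscle strength in a maximum hand grip strength test". Neither is ranked above the other.

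Under Sample size calculation and statistical analyses, one method serves the primary comparison: "Treatment effect will be assessed by unpaired comparison of both treatment arms for the change from baseline using the Student t-test". One threshold follows: "A significance level of α < 0.05 will be specified to indicate statistical significance". It does not say whether the test is one-sided or two-sided.

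The same section sets the size of the trial: "A total of 110 patients is planned to be enrolled in the study", and "A sample size of 55 in each group will have 80 % power to detect a clinically relevant difference". The difference is given in numbers for one endpoint only: "Rivermead Motor Assessment Gross Function scale improvement between the groups of 1.5 points". Hand grip is added to that sentence as a clinically relevant improvement without a figure. No standard deviation is given for either endpoint.

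The article contains no alpha split, testing order, gatekeeping step or rule on how many endpoints must be significant. Two places link the domains with "and": the first hypothesis in the Background, which joins muscle function with physical performance, and the power sentence. Neither is a decision rule.

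**The concern.** With two primary endpoints, a significance level is complete only when the plan also says which pattern of results counts as success. Here it does not. If RMA is significant and hand grip is not, or the reverse, the article does not say whether the trial met its primary objective. Whoever writes the conclusion would then decide with the results in view, and blinding of treatment does not prevent that.

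The two possible answers fail in different ways. If one win is enough, two tests at an unadjusted 0.05 do not hold the overall error at 5%. If two wins are needed, the error is held, but the power that matters is the chance of winning on both, and the article gives no figure that is clearly that one.

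**Working it through.** **Inputs from the article.** Two primary endpoints; alpha 0.05, stated once; 55 per group; 80% power; RMA difference 1.5 points.

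**Assumptions, because the article is silent.** Two-sided tests; 0.05 applied to each endpoint; correlation between the two test statistics from 0 to 0.9; where power is needed, 80% for each endpoint.

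**1. The plan's own figure.** The 55 per group cannot be reproduced, because no SD is stated. It can only be inverted: SD = 1.5 / [(z for alpha + z for power) × √(2/55)].
- Two-sided 0.05: 1.5 / [(1.960 + 0.842) × 0.1907] = 2.81 (2.78 with the noncentral t).
- One-sided 0.05: 3.16.
- Two-sided 0.025: 2.55.

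The sample size alone therefore does not show which alpha was used. For hand grip, with neither a difference nor an SD, not even this inversion is possible.

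**2. If either endpoint suffices.** Familywise error = 1 − P(|Z1| < 1.96 and |Z2| < 1.96). At correlation 0 this is 1 − 0.95² = 0.0975. From the bivariate normal distribution:

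| Correlation | Familywise error, 0.05 each |
|---|---|
| 0 | 9.75% |
| 0.3 | 9.5% |
| 0.5 | 9.1% |
| 0.7 | 8.3% |
| 0.9 | 7.0% |

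Positive correlation lowers the rate, but even at 0.9 it exceeds 5%. Counting only false claims of benefit, the rate at correlation 0 is 1 − 0.975² = 4.9%, against a nominal 2.5%.

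**3. If both must succeed.** With both nulls true, the chance that both tests are significant is 0.05² = 0.25% at correlation 0 and 0.9% at 0.5. With only one null true it cannot exceed 5%. Type I error is therefore controlled. Joint power, given 80% for each endpoint, is 0.80² = 64% at correlation 0, 69% at 0.5 and 71% at 0.7.

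**4. Cost of adjusting.** At 0.025 per endpoint (Bonferroni, or the first step of Holm), familywise error is 1 − 0.975² = 4.9% at correlation 0 and 4.7% at 0.5. If the 80% was computed at two-sided 0.05, the expected test statistic is 1.960 + 0.842 = 2.802. Power for a given endpoint at 0.025 is then Φ(2.802 − 2.241) = Φ(0.560) = 71%. Keeping 80% at 0.025 needs 55 × [(2.241 + 0.842)/2.802]² = 66.6, so 67 per arm (134 in total). In a fixed sequence the first endpoint keeps the full 0.05 and its power does not change.

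**The case against.** A reader might infer that the trial's false-positive rate nearly doubles. The article does not support that as a statement of fact. It nowhere says that one win is enough, and the only wording that links the two endpoints is conjunctive. If both are required, there is no inflation at all. That 0.05 applies in full to each endpoint is itself inferred from a single alpha sentence, and two-sidedness and every correlation used above are assumptions. This part of the objection stands, and it makes the size of the problem conditional.

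It can also be said that multiplicity rules often sit in the full protocol or analysis plan, neither of which is shown. That is a fair limit: those documents may hold a rule. But the article does fix the number of primary endpoints, the test, the significance level, the sample size and the power. Taken together, these do not define a primary claim with both 5% error and 80% power under either reading, unless the 80% was already meant jointly. That cannot be checked without SDs and a grip difference.

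Finally, putting RMA first in a sequence imposes a ranking that the article does not give, and the study title stresses muscle strength, which hand grip measures. This also stands. RMA first is a defensible choice, not the only one.

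**Conclusion.** The point holds in conditional form. The article sets two primary endpoints against one unadjusted 0.05 level and does not say how they combine.

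- If either suffices, the familywise error is about 9.8% at most, and between 9.1% and 7.0% for correlations from 0.5 to 0.9.
- If both are required, error is controlled, and joint power is about 64% to 69% for correlations from 0 to 0.5, if the stated 80% is per endpoint.

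Near-doubling of the error rate is the upper end of the first reading, not a property of the plan as such. What is certain is that the article does not settle what a split result would mean. That bears on the trial's main conclusion, so a written rule is needed whichever reading was intended.

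**What to change.** Before unblinding, replace the single alpha sentence with one of the following rules, and state that tests are two-sided.

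- **Endpoints of equal rank: Holm.** The smaller p-value must fall below 0.025; if it does, the other endpoint is tested at 0.05. Cost: power for a given endpoint at the 0.025 step is about 71%, if the 80% was computed at two-sided 0.05.
- **Ranked endpoints: fixed sequence.** Test RMA change at 4 weeks first at 0.05, since it is the only endpoint with a stated difference; its power is unchanged. Test hand grip at 0.05 as confirmatory only if RMA is significant; otherwise report it descriptively. Cost: hand grip cannot be claimed if RMA fails.
- **Both required.** Declare success only if both endpoints are significant at 0.05. No alpha split is needed. Cost: the power statement must be restated as joint power, which requires a hand grip difference and SDs for both endpoints.

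The change is one or two sentences and needs no new data. Extra patients arise only if the sponsor wants to restore 80% power under Holm or the both-required rule.

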## Discussion

The present AMINO Stroke study will be the first randomized double-blinded trial investigating an effect of essential amino acids (EAAs) on skeletal muscle functional capacity, muscle mass, muscle strength and physical performance in early post-stroke rehabilitation. In addition, the effect of EAAs supplementation on stroke-related quality of life, nutritional status, activities of daily life and outcome will be evaluated.

An improvement of physical and functional performance in stroke patients is expected after participating in 4-weeks rehabilitation program [32]. In the present study we expect a beneficial impact of the dietary supplementation of the EAA on skeletal muscle function and muscle mass during post-stroke rehabilitation.

The benefit of EAAs supplementation on skeletal muscle has been shown in several studies in elderly individuals. Thus, an elevated level of muscle protein synthesis was dependent on the availability of EAAs in a dose-depended manner [33]. An experimental study performing in the young adults revealed an increase of leucine incorporation into the skeletal muscle proteins under administration of EEAs as a flooding dose [34]. Ingestion of EAAs shortly after exercise enhanced muscle protein synthesis in older adults, indicating a combination of EAAs with exercising as a sufficient therapy for the treatment of muscle wasting [35]. Another study showed an improvement of lean mass, muscle functional capacity and muscle strength after 16 weeks supplementation of EAAs and arginine in healthy elderly individuals [36].

A reduction of the muscle mass might be directly depending on a limited availability of the EEAs and other nutrients [14]. Impaired feeding which results in malnutrition is frequently observed in patients with dysphagia after stroke [37]. About 50 % of stroke patients have feeding difficulties due to dysphagia [38]. In older patients reduced nutritional status might be observed already at hospital admission with the diagnosis of acute stroke [39]. Patients with lower body weight have been observed to have worse fatal and non-fatal outcome after stroke [40]. While the inverse association of overweight and improved outcome has previously been termed obesity paradox [41], the perception advanced towards an obesity paradigm, acknowledging the protective overweight in cardiovascular disease [42].

Malnutrition and sarcopenia are often reported in the rehabilitation setting [43, 44]. Therefore, we believe that supplementation of the EAAs will contribute to attenuation of muscle wasting and improve skeletal muscle recovery [45]. There are a number of methods available to assess muscle mass [46]. In the present study muscle mass will be estimated by using BIA that provides information to integrity of cell membrane and tissue interfaces, intracellular and extracellular fluid distribution, body fat and body lean mass [31, 47]. Previously, a strong correlation between muscle mass assessed by BIA and magnetic resonance imaging has been shown [48]. The prevalence of sarcopenia using BIA measurements has been repeatedly examined in elderly [49, 50], and in patients with neuromuscular or cerebrovascular disease [51, 52]. Therefore we believe that BIA is an appropriate method for muscle mass assessment.

In Germany, stroke has not been selected for chronic disease management programs so far [53]. Post-stroke rehabilitation is usually recommended to start immediately following hospital discharge. The so called early post-stroke rehabilitation phase includes about 4 weeks. Mainly, recommendations given in discharge letters from acute care hospitals are frequently focusing on medical treatments [53]. At present, post-stroke management does not include monitoring of muscle mass, muscle strength and muscle function. The European stroke guidelines do not consider post-stroke muscle wasting as a relevant complication [54]. However, recognition of this problem through the medical community might improve the long-term outcome after stroke.

## Abbreviations

EEA: Essential amino acid
BI: Barthel Index
EQ-5D: Quality of life questionnaire
RMA: Rivermead motor assessment
MAS: Motor assessment scale
FAC: Functional ambulation category
SPPBT: Short physical performance battery test
MNA: Mini nutritional assessment
SGA: Subjective global assessment
BIA: Bioelectrical impedance analysis
SM: Skeletal muscle
